## Abstract

**Background:**

E-health tools are a new mechanism to expand patient care, allowing supplemental resources to usual care, including enhanced patient-provider communication. These applications to smoking cessation have yet to be tested in a hospitalized patient sample. This project aims to evaluate the effectiveness and cost-effectiveness of a tailored web-based and e-message smoking cessation program for current smokers that, upon hospital discharge, transitions the patient to continue a quit attempt when home (Decide2Quit).

**Design:**

A randomized two-arm follow-up design will test the effectiveness of an evidence- and theoretically-based smoking cessation program designed for post-hospitalization.

**Methods:**

A total of 1,488 patients aged 19 or older, who smoked cigarettes in the previous 30 days, are being recruited from 27 patient care areas of a large urban university hospital. Study-eligible hospitalized patients receiving usual tobacco cessation usual care are offered study referral. Trained hospital staff assist the 744 patients who are being randomized to the intervention arm with registration and orientation to the intervention website. This e-mail and web-based program offers tailored messages as well as education, self-assessment and planning aids, and social support to promote tobacco use cessation. Condition-blind study staff assess participants for tobacco use history and behaviors, tobacco use cost-related information, co-morbidities and psychosocial factors at 0, 3, 6, and 12 months. The primary outcome is self-reported 30-day tobacco abstinence at 6 months follow-up. Secondary outcomes include 7-day point prevalence quit rates at 3-, 6-, and 12-month follow-up, 30-day point prevalence quit rates at 3 and 12 months, biologically confirmed tobacco abstinence at 6-month follow-up, and multiple point-prevalence quit rates based on self-reported tobacco abstinence rates at each follow-up time period. Healthcare utilization and quality of life are assessed at baseline, and 6- and 12-month follow-up to measure program cost-effectiveness from the hospital, healthcare payer, patient, and societal perspectives.

**Discussion:**

Given the impact of tobacco use on medical resources, establishing feasible, cost-effective methods for reducing tobacco use is imperative. Given the minimal hospital staff burden and the automated transition to a post-hospitalization tailored intervention, this program could be an easily disseminated approach.

**Trial registration:**

Current Intervention Trial NCT01277250

## Background

The health effects of smoking tobacco and their economic impact are well documented 
[1]. Alabama’s tobacco smoking prevalence rate of 22.5% 
[2] exceeds the national average of 19.8% 
[3], with expected higher rates among hospitalized patients 
[4,5]. Tobacco cessation studies have demonstrated that proactive recruitment of patients for smoking cessation counseling engages a larger percentage of patients, and intensive counseling with at least 1-month follow-up post-hospitalization is effective 
[6], with 3-months follow-up found even more effective 
[7]. However, even longer duration counseling in-hospital, without follow-up, was not found more effective 
[6]. Together, this suggests that, while hospitalization is an opportunity to introduce smoking cessation, post-discharge follow-up is essential.

In *Crossing the Quality Chasm*, the Institute of Medicine began to emphasize that care should not occur just within face-to-face visits but that ‘access to care should be provided over the internet’ to foster continuous healing relationships 
[8]. Subsequent reports 
[9-11] and other groups 
[12], including the Centers for Medicare and Medicaid Services 
[13], have continued to support the concept of e-Health tools to increase patient access, motivate patients in their care, and re-engineer patient-centered care. Because of time constraints on providers, and with over 70 million Americans using the internet to access health-related information 
[14], computer- and internet-based tools are becoming widespread. Even in Alabama, with its low ranking on digital access, 61.7% of households have internet access with additional access through work or community resources 
[15]. Innovative supplemental e-resources are being created to augment brief tobacco-cessation counseling. These new web-based tools/programs present a unique opportunity to enhance continued smoking cessation for hospitalized patients after discharge.

Secure patient-provider e-messaging systems have been found to improve patient satisfaction and increase practice efficiency while maintaining HIPAA standards 
[16,17]. The strategy of combining e-coaching and computer-automated tailored information has been shown to be successful 
[18]. Though these innovative web-based tools/programs present a unique opportunity, reports of web-based interventions for hospitalized smokers are limited 
[6] and no reviews or meta-analyses that included such programs had been found at the time of writing this manuscript 
[19,20].

In a meta-analysis, 17% of web- and computer-based smoking cessation out-patient interventions were found effective in doubling quit rates at 6 months among general population participants compared to controls 
[19]. Also, treatment effects for web-based smoking cessation interventions appear fairly stable over time, as a meta-analysis found cessation rates did not dissipate at subsequent follow-ups 
[21]. While many of the web-based smoking cessation programs are appropriate for any smoker, they may miss an opportunity to address specific relevance of smoking to the smoker’s recent hospitalization and the unique needs of the smoker in care-transition. For this reason, we have enhanced an existing web-based smoking cessation program to address individualized post-hospitalization smoking-cessation needs through e-messages.

## Methods/Design

### Study design

This study uses a randomized controlled two-arm multiple follow-up design to: (1) test the effectiveness of the Decide2Quit intervention against usual smoking cessation care for hospitalized patients transitioning to outpatient care; and (2) determine the cost-effectiveness of each component of a smoking cessation intervention for hospitalized smokers (the Decide2Quit post-hospital intervention and usual care). The primary outcome for effectiveness is self-reported 30-day point prevalence at 6 month post-hospitalization. Secondary outcomes are: biologically confirmed smoking cessation at 6 months; 30-day point prevalence at 3 and 12 months; and 7-day point prevalence at 3, 6, and 12 months. Consecutive abstinence will be assessed using the three 30-day point prevalence data. The cost-effectiveness of the intervention compared to usual care will be determined by considering costs of intervention implementation and costs of healthcare with effectiveness measured in terms of Quality Adjusted Life Years (QALYs).

This study has obtained approval from The University of Alabama at Birmingham (UAB) Institutional Review Board for Human Use (IRB). All study personnel are IRB trained and Health Insurance Portability and Accountability Act (HIPAA) certified.

### Setting and sample

The setting for this study is UAB Hospital, a 1,000 bed state-of-the-art academic center hospital with 43 patient care areas (PCAs). Of these, 27 PCAs serve patients potentially eligible for study participation. The 16 PCAs not included in this study, maternity and palliative care units and some intensive care and psychiatric units (acute, dementia, and adolescent care), are excluded due to the difficulty of obtaining informed consent and/or the unique smoking cessation needs among the patients served. As well, we will over-recruit smokers with pulmonary and cardiac diseases, as this population is of primary interest to the study collaborative. While UAB Hospital has a non-smoking policy, and patients are expected to abstain from tobacco use while hospitalized, non-adherence to this policy has been noted in patients sufficiently mobile to go outdoors.

The UAB Lung Health Center staff receive a daily report of all current smokers admitted to UAB Hospital during the previous 24 h to provide or facilitate the provision of tobacco cessation usual care at bedside (see Table 
1 for description of this component). After provision of usual care bedside, all potentially eligible patients admitted to the selected PCAs between July 2011 and May 2013 will be given the opportunity to learn about the study and enroll. To be eligible for the study, a patient must meet the following criteria: (1) over the age of 18; (2) a current smoker defined as at least one puff in the past 30 days; (3) read and speak English; (4) able to provide meaningful responses to the screening questions and to provide informed consent; (5) have an email address and internet access through self or surrogate; and, (6) not have another household member participating in the study. In addition, patients under isolation precautions, except for contact isolation only, are not approached for participation. Criteria 2, 4 and 6 are common to all CHART sites.

**Table 1 T1:** Intervention and usual care contacts by type, timing, and instigator

	**Type of contact**	**Timing**	**Instigator**	
Usual Care - all patients	Admission booklet page on smoking	At admission	Hospital admitting staff	
	Smoking Cessation local resources handout and brief counseling	During hospital stay	Lung Health Center staff	
	Smoking cessation information in discharge packet^a^	At discharge	Hospital assigned nurse	
Additional Components for those randomized to Intervention	Website registration and orientation	Prior to discharge	Hospital Quit Staff	
	Tailored e-mails	Weekly for 12+ weeks^b^	Automated by web-system	
	Telephone call	7 to 14 days post-discharge	Hospital Quit Staff	
	Secure messaging	At will	Participant or Quit Advisor (Tobacco Treatment Specialist)	
	Website use	At will	Participant	

^a^A portion of which is provided optionally at the discretion of the hospital-assigned nurse.

^b^Minimum of 12 weeks, longer if participant changes their readiness to quit status.

### Participant recruitment and randomization to condition

Study staff verify eligibility with a screening assessment that includes questions about internet access and use of e-mail, the participation of other household members in this study, and mental status (if in question). Eligible patients are provided an overview of the study and a chance to ask questions prior to providing written informed consent. After completion of baseline assessments and listing on the electronic study roll by study staff, patients are randomized to study condition (intervention or usual care). Blocked randomization within each PCA is used to reduce selection and accidental bias and achieve balance in the allocation of participants to treatment arms. The study statistician generated random number lists for each PCA prior to study initiation. The Study Coordinator identifies the participants to randomize to study condition each day based on their order of listing on the study roll and the allocation indicated for the PCA in which they were recruited. As participants are allocated to the intervention arm, the Study Coordinator sends email alerts to designated hospital staff (Quit Staff) that newly randomized patients need to be registered to the intervention website, Decide2Quit. Figure 
1 depicts the recruitment and initial study activities flow.

**Figure 1 F1:**
[figure not shown]
Participant eligibility and recruitment flow.

### Intervention description

The intervention includes tailored e-mail messages and an interactive website (Decide2Quit) designed for post-hospitalization smoking cessation which allows secure messaging with a certified Tobacco Treatment Specialist (TTS) (Quit Advisor) and both in- and post-hospital contact by the hospital Quit Staff. The Quit Staff visit patients assigned to the intervention arm at bedside to assist them with registration to Decide2Quit using secure laptops connected to the website via the hospital’s WiFi system. The Quit Staff then orient the participants to the website by displaying general content areas and available quit tools. Participants also receive a booklet illustrating how to access and navigate the website. In addition, this booklet features study contact information for technical problems, blank copies of the website ‘quit plan’ , and a letter for their primary healthcare provider. This letter contains study-related information and requests the healthcare provider’s verbal and pharmaceutical (as appropriate) support of their patient’s quit attempt.

Some patients randomized to the intervention are discharged from the hospital before the Quit Staff can visit them to provide website registration and orientation. The print materials are mailed to these participants and Quit Staff provide telephone assistance with website registration and orientation. The Quit Staff make one follow-up telephone contact, at 7 to 14 days post-discharge, to encourage website use in the context of the primary area of health concern the participant identified at website registration.

### Theoretical framework and intervention e-messages

Two behavioral change theories are the basis for both the website content and e-mail messages: Social Cognitive Theory 
[22] and the Transtheoretical Model 
[23]. Two types of email messages are sent: tailored to stage of change and tailored to health concern. Stage of change messages are framed to address where each participant has self-identified along the quit continuum, from no interest in quitting to already quit. For example: those with no interest in quitting receive messages containing information about benefits to quitting and harm reduction; those actively trying to quit receive messages that promote self-efficacy to avoid smoking situations and overcome cravings; and, those already quit receive messages targeting relapse prevention. Participants confirm or change their smoking stage status at each website login. While a set number of messages are available for each stage, when the participant changes their stage, messages ‘start over’ with the messages for the new stage, thereby increasing the total number of messages sent.

The health concern messages, sent weekly for 12 weeks, are based on the primary area of health concern identified by the participant at website registration (cancer, lungs disease, heart disease or stroke, surgery or wound healing, or none of these). E-mail messages provide general information related to the selected health concern, without specifying protected health information. Outcome expectations and other theoretical constructs provide the basis for the messages. For example, someone selecting ‘surgery or wound healing’ would receive the message ‘Quitting smoking allows more blood with oxygen to reach wounds to help them heal faster’ while someone selecting ‘heart disease or stroke’ would receive ‘In just one day of quitting, you will have started to lower your risk of having a heart attack. Every day you stay quit, you lower your risk of having a heart attack more.’ Those choosing ‘none of these’ receive general health messages. Each message ends with promoting website use by providing the link to ‘learn more about ____'. Table 
1 summarizes the intervention contacts.

### Web-site content

This intervention website is a modification and refinement of an existing version of Decide2Quit which is the product of two Investigators’ prior NIH-funded research efforts to develop web-delivered smoking cessation systems for patients 
[24] and providers 
[25]. The website continues to include an interactive quit-support calculator (questionnaire with feedback focusing on decisional balance, triggers, risks, and smoking-related symptoms), models for communication with health providers and family members, educational materials, a secure messaging system to access a TTS (Quit Advisor), and access to a social network of online smokers (BecomeAnEx). The current site has been expanded and tailored to better serve the unique needs of recently hospitalized adult smokers by providing information on how quitting reduces specific health risks, and the temporary physical and emotional side effects of quitting. The administrative side of the website includes the ability to track patient web activity and smoking status, document follow-up phone calls by the Quit Staff, and monitor participant-generated messages to the Quit Advisor (using the compose function on a secure, HIPAA-compliant messaging system using Secure Socket Layer technology and hosted on a separate server used exclusively for Decide2Quit). Thus, the intervention has both patient-facing and administrative components.

### Identifying and training hospital staff

Meetings with various hospital staff groups led to the identification of respiratory therapists as the most appropriate hospital staff (Quit Staff) for this study given their professional role in lung health and their hospital-wide duties. When the respiratory therapists’ duties preclude assisting with patient registrations, a hospital-paid smoking cessation staff provides this service. Quit Staff provided input into the development of the administrative portal they use to track contact with intervention participants, as well as practical suggestions for how best to implement this intervention in UAB Hospital. Quit Staff training includes a didactic overview of the study, information on specific protocols (registration, orientation, and follow-up telephone contact) and the website, and a hands-on computer training for the website, from both the patient and administrative perspectives.

### Data collection and measurements

Survey data collection takes place at the hospital bedside for baseline and via telephone interview for the 3- , 6- and 12-months follow-up. Additional biologic measures are collected at 6-month follow-up as described below. Tables 
2 and 
3 describe the measures to be collected at each time point. Measures are noted as Tier 1 (core across all collaborative projects), Tier 2 (optional measures, standard across projects), or Tier 3 (specific to this project). Study staff who conduct assessments are blinded to participant condition and are trained to collect all data uniformly according to written protocols. Data are entered directly into an internet-based survey system using security-enabled laptop computers with either WiFi (at bedside) or hard-wired internet access. All questions require responses by the system to facilitate complete datasets (‘refused’ and ‘does not know’ response options available). Study staff are trained to complete paper copies should there be difficulty in accessing the internet, with the study data manager later entering the data into the database. Some data are acquired from patients’ electronic medical records, study records, or outside sources, as noted in Table 
3.

**Table 2 T2:** General assessments and time-points

**Tier**^**a**^	**Measure**	**Details**	**Month**			
			**0**^**b**^	**3**	**6**	**12**
1	Demographics^c^	Age, length of stay, insurance, height, weight, ICD-9 codes, DRGs, Procedure codes, admission type, discharge ‘to’ plan, race, ethnicity, gender, education, marital status, other household smokers,	X			
1	Smoking status	Self-reported - last 7 days		X	X	X
1	Smoking status	Self-reported - last 30 days	X	X	X	X
3	Smoking status	Prolonged abstinence (multiple point prevalence)		X	X	X
1	Quit plan	Post-hospital plans regarding quitting	X			
1	Other tobacco use	Other than cigarettes-last 30 days	X	X	X	X
2	Tobacco dependence	Heavy Smoking Index (2 questions)	X	X	X	X
2	Tobacco cessation treatments	Behavioral and pharmacologic treatments, dose/frequency, length of use	X		X	X
3	Pack-history	Lifetime	X			
3	Longest abstinent period	Lifetime at 0 months; past year at 12 months	X			X
1/3	Satisfaction	Satisfaction with smoking cessation help		X		
3	Quit attempts	Past year (over 24 h abstinent)	X		X	X
3	Social support	Perceived support from significant others to quit/abstain	X		X	X
3	Internet and e-mail use	Frequency and type of use	X			
1	Self-efficacy for abstinence	Single question	X		X	X
3	Self-efficacy for abstinence	SEQ12	X		X	
2	Alcohol use	Audit-C	X		X	X
2	Depressive symptomology	PHQ-2	X		X	X
2	Saliva cotinine, exhaled CO, surrogate corroboration^d^	Validate 7-day smoking status			X	

^a^Tier 1 = common to all CHART trials, Tier 2 = common among some CHART sites, Tier 3 = this site only.

^b^Month 0 = Baseline.

^c^Some data collected after hospital discharge from electronic medical records and discharge summaries.

^d^Randomly selected sample of past-7-days smokers and all past-7-days non-smokers.

**Table 3 T3:** Data collection for cost effectiveness analysis

**Cost**^**a**^	**Tier**	**Data item**	**Description**	**Valuation**			
Cost of usual care	1	LHC staff time	LHC staff time spent at bedside	Average time per patient			
	1	Hospital nurse time	Time spent by assigned nurse assembling discharge packet (containing usual care)	Average time per patient			
	1	Materials	Cost of printing	Actual costs			
Cost of intervention	1	Hospital Quit Staff training	Time of trainers and trainees, materials, and so on	Study records			
	1	Hospital Quit Staff time	Time spent on each patient in preparation, implementation, and documentation of website registration/orientation and 7-14 days post-discharge follow-up call	Average time per patientWeb tracking			
	1	Quit Advisor time	Time spent on each patient in preparation, implementation, and documentation of responses to patient-generated messages	Average time per message			
	1	Patient materials	Brochures, booklets, and so on	Study records			
	1	Web site implementation (not development)	(To be determined, though may contain maintenance, servers, programming, content updating, emailing, and so on)	Study records			
	1	Time of participant on website	Time recorded on website per personal login; number, frequency, and content of messaging to Quit Advisor through the *Decide2Quit* website	Website tracking			
				Month/Source			
				0	3	6	12
Healthcare-related costs	2	Health care utilization	Hospitalizations, outpatient visits, procedures, Emergency Room visits (last 6 months) (No/Yes - # times)	X		X	X
	2	Time cost related to care	Time (hours) off work for participant and others who accompany participant to visits	X		X	X
			Gender-age group average wages for the state	Bureau of Labor Statistics			
	2	Out-of-pocket (OOP) costs	Copayments, deductibles, transportation, parking, meals, and so on (including caregivers, when applicable) (last 6 months)	X		X	X
	2	Costs to health care payers	Reimbursements to health care payers according to type of care	Hospital bills / Medicare reimbursements			
	2	Medicines	Copayments, deductibles, OOP costs (last 6 months)	X		X	X
			Wholesale price for health care payers	Red Book			
Smoking cessation products / programs costs	3	OOP costs	Co-payments, and so on. (last 6 months)	X		X	X
	2	Reimbursements	Reimbursements for health care payers	TBD			
Quality of life	2	EQ-5D-5L [26]		X		X	X
	3	SF-12		X		X	X

^a^All costs will be expressed in the same year of currency.

### Biologic measures

At 6-month follow-up, participants are contacted by telephone and asked about their past-7-days’ smoking status. Participants reporting not smoking in the past 7 days and living within a 40-min commute are asked to come to the clinic for in-person saliva collection, for cotinine testing, as well as a Carbon Monoxide (CO) measure. Those living farther away are mailed saliva collection kits as described in the CHART biochemical verification study (see Riley *et al*. CHART Overview paper). A random sample of self-reported past-7-day tobacco users are asked to provide saliva samples in the same manner as non-smokers. For past-7-days smokers, study staff check a random selection list to determine if the participant is selected to provide a biologic specimen. We anticipate this sample to be about 10% of the past-7-days smokers. At the time of the telephone interview, those participants who are to provide in-person biologic measures are scheduled to come into the clinic within the following 2 weeks. If a participant misses two scheduled clinic appointments, a saliva kit is mailed with follow-up attempts the same as for all mailed kits.

The primary biologic measure is saliva cotinine measurement. Salivary cotinine is considered a very sensitive measure for determining smoking status 
[27,28]; a level of <15 ng/mL confirms abstinence 
[29,30]. Exhaled air CO levels in exhaled air are measured with a Bedfont Smokerlyzer; a level of <10 parts per million confirms abstinence 
[31]. CO is considered the primary biological confirmation measure when the saliva cotinine measure is considered potentially invalid due to current use of nicotine replacement therapy or alternate tobacco products. If a selected participant is unable to attend the 6-month in-person visit, every attempt is made to collect the specimen by mailed saliva sample kit or home visit (or other mutually agreed upon meeting place) by study staff. When no biological measure can be acquired from a participant, study staff attempt corroboration of self-reported smoking status from another person (contact information and permission to contact provided by participant at previous contact).

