## Discussion

There is considerable research on smoking cessation among outpatients and among inpatients with respiratory or cardiac disease. However, for general inpatient smokers, there is little information on programs that transition to post-hospitalization and most have follow-up limited to less than 6 months. Rates of smoking cessation immediately post-hospitalization are high, but relapse rates are also high 
[47]. Conceptually, relapse prevention should begin in the hospital and continue after discharge, as the crucial time for relapse occurs 1 week after quitting 
[48]. For many patients, this is concurrent with discharge and the return to a smoking-related routine with deeply engrained smoking-related behaviors 
[6]. Despite this knowledge, cessation interventions designed to transition patients from hospital to home have not widely diffused into usual clinical practice. This study will add to the limited literature about smoking cessation in the general inpatient population as well as smoking status at 12 months post-hospitalization.

Identifying appropriate hospital staff to register patients for a smoking cessation program was a challenge in the current healthcare system. A strong interest in tobacco cessation and access to and familiarity with all areas of the hospital are considered essential. As hospital resources, environments, and staffing vary, different hospital personnel may be identified as most appropriate. After discussions with personnel on many levels and areas of this hospital, respiratory therapists were identified as the best fit. Regardless, having committed champions among the hospital staff, or even better dedicated hospital staff, is imperative for successful implementation and the institutionalization that leads to program sustainability.

Given the unknown validity of self-reported health behaviors and the expense and difficulty of collecting biological specimens, this study also aims to determine the validity of self-reported smoking status for both self-reported quitters and non-quitters post-hospitalization. Participants are not informed of their selection for biological confirmation until after their quit status is assessed via telephone. We anticipate these findings will provide an algorithm for estimating true rates of smoking status from self-reported rates in future studies, increasing confidence in findings while reducing costs and allowing more precise measures of cost-effectiveness.

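### The specimen can be taken 2 weeks or more after the 7-day telephone report it validates, so a change in smoking after the call can be counted as misreporting

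*Protocol article*

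**What the plan says.** All of this is in the protocol article.

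- **The report.** Biologic measures: "At 6-month follow-up, participants are contacted by telephone and asked about their past-7-days’ smoking status".
- **The purpose of the specimen.** Table 2 (Data collection and measurements) describes cotinine, exhaled CO and surrogate corroboration at month 6 as "Validate 7-day smoking status". All reported non-smokers and a random sample of reported smokers (about 10%) are tested.
- **The timing.** For clinic participants, "those participants who are to provide in-person biologic measures are scheduled to come into the clinic within the following 2 weeks". After that, "If a participant misses two scheduled clinic appointments, a saliva kit is mailed with follow-up attempts the same as for all mailed kits". For distant participants, "Those living farther away are mailed saliva collection kits as described in the CHART biochemical verification study"; that source is not part of the article, and no time limit is given here.
- **The decision rule.** For saliva cotinine, "a level of <15 ng/mL confirms abstinence"; for exhaled CO, "a level of <10 parts per million confirms abstinence". CO takes over where current nicotine replacement or other tobacco use makes cotinine unreliable. The article does not say when that use is asked.
- **The use made of the result.** Biologically confirmed cessation at 6 months is a secondary outcome (Study design). The Discussion adds that "this study also aims to determine the validity of self-reported smoking status for both self-reported quitters and non-quitters post-hospitalization", and expects an algorithm for estimating true smoking rates in future studies. It also says that participants learn of their selection for testing only after giving their status by telephone.

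**The concern.** The permitted interval between report and specimen is at least twice the 7-day window being validated. Someone who truthfully reported abstinence and then smoked would be scored as a false reporter. A sampled smoker who stopped after the call would look wrong the other way. Someone who wrongly denied smoking knows of the test before it is taken and could abstain for it. Without a smoking report dated to the specimen, the data cannot separate these cases from true misreporting.

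The validity aim is most exposed, because its product is a correction algorithm meant for other studies. The absolute level of confirmed abstinence is exposed too.

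**Working it through.** **Step 1. Does the plan's own figure depend on this?** The Power estimate section gives a detectable difference of 5.12 points with 744 per arm, 12% in the comparison group, two-sided alpha 0.05 and 80% power. A two-proportion calculation with pooled variance for 12% against 17.12% returns 744 per arm and power 0.800, so the figure reproduces. It concerns self-reported 30-day abstinence, which uses no specimen, so the lag does not change it.

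**Step 2. Overlap of the two windows.** Input: a 7-day report at the call and a specimen at lag L days. I assume that the specimen speaks to the 7 days before it, since the article gives no look-back period for either marker. Shared days = max(0, 7 − L).

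| Lag (days) | 0 | 3 | 5 | 7 | 10 | 14 |
|---|---|---|---|---|---|---|
| Shared days | 7 | 4 | 2 | 0 | 0 | 0 |

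A specimen within the first week overlaps in part. From day 7 on there is no overlap, and the clinic schedule allows lags up to day 14.

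**Step 3. Truthful abstainers disconfirmed.** The article gives no relapse rate for people abstinent at 6 months. I assume a monthly rate h of 5% to 15%. Share relapsing by lag L = 1 − (1 − h)^(L/30).

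| Lag (days) | h = 5% | h = 15% |
|---|---|---|
| 7 | 1.2% | 3.7% |
| 14 | 2.4% | 7.3% |
| 28 (illustrative; not in the article) | 4.7% | 14.1% |

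**Step 4. Effect on the validity estimate.** Let m be the true misreport rate among reported quitters and r the share of truthful reporters who relapse before the specimen. Apparent misreport = 1 − (1 − m)(1 − r). With m = 15% (assumed):

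- r = 5%: 1 − 0.85 × 0.95 = 19%
- r = 10%: 1 − 0.85 × 0.90 = 24%
- r = 20%: 1 − 0.85 × 0.80 = 32%

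The 14-day values from Step 3 give a smaller shift: 1 − 0.85 × 0.976 = 17% and 1 − 0.85 × 0.927 = 21%.

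**Step 5. Effect on confirmed abstinence.** For illustration, apply the planning rates of 12% and 17.12% to the confirmed outcome; each becomes p(1 − r).

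| r, control / intervention | Confirmed rates | Difference (points) | Risk ratio | Power |
|---|---|---|---|---|
| 0 / 0 | 12.0% vs 17.1% | 5.1 | 1.43 | 80% |
| 5% / 5% | 11.4% vs 16.3% | 4.9 | 1.43 | 78% |
| 10% / 10% | 10.8% vs 15.4% | 4.6 | 1.43 | 75% |
| 20% / 20% | 9.6% vs 13.7% | 4.1 | 1.43 | 69% |
| 10% / 5% | 10.8% vs 16.3% | 5.5 | 1.51 | not computed |
| 5% / 10% | 11.4% vs 15.4% | 4.0 | 1.35 | not computed |

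Equal relapse lowers the absolute rates and the difference but leaves the ratio alone. The ratio moves only when relapse differs by arm. Abstaining before a known test pushes the other way and cannot be sized from the article.

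**The case against.** The strongest case on the other side is that a condensed article need not describe the visit form. A reader might infer that the smoking question is not repeated at collection, but the article is only silent. It leaves the kit procedure to a separate paper. The columns of Table 2 are months, not contacts, and three smoking-status rows are marked at month 6, so the table cannot exclude a repeat. The marker rule also needs current nicotine replacement use, which suggests that something may be asked near collection. This stands: the supportable statement is that no repeat is described. The 2-week schedule, however, is stated outright.

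Three further readings are tempting and not supported.

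- **That the $100 rewards stopping before the test.** Participant incentives pays for providing a clinic sample whatever the result, and selected smokers are sampled in the same way.
- **That the Discussion shows high relapse at this stage.** Its remark concerns the period just after hospitalization, not people abstinent at 6 months.
- **That the trial's main comparison is compromised.** The primary outcome is 30-day self-report, while the specimen addresses 7-day status. The article gives no reason to expect post-call change to differ by arm.

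There is also a sound objection to one obvious remedy. The report is deliberately taken before participants know of the test, and its validity is the aim. Judging the specimen against an answer given at collection would replace an unprompted report with one made in the knowledge of testing. It would also let a false reporter explain a positive result as smoking since the call. This stands, and it shapes the fix.

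**Conclusion.** The point holds as a limited design weakness. The stated call-to-specimen interval exceeds the window being validated, and from day 7 the two weeks do not overlap. Unless status is re-asked at collection, behaviour change after the call is counted as misreporting.

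The size rests on assumptions. At monthly relapse of 5% to 15%, between 1.2% and 3.7% of truthful abstainers would be disconfirmed at 7 days and 2.4% to 7.3% at 14 days. The 14-day figures put everyone at the scheduling maximum, so the average over clinic visits kept on schedule would be lower. Mailed kits may run longer, but the article gives no figure. Because temporary abstinence before the test acts in the opposite direction, the net direction is unknown. An algorithm for other studies should not carry two opposing errors of unknown size.

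**What to change.** First state whether smoking status is already re-asked at collection. If it is not:

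1. At each clinic or home specimen, and on a dated card in each mailed kit, ask past-7-day smoking, date of last cigarette, and current nicotine-replacement and other-tobacco use. Record the specimen date.
2. Keep the telephone report, given before participants know of the test, as the report being validated.
3. Use the specimen-day answer in a supplementary analysis to flag possible change since the call, without automatically clearing those cases of misreporting.
4. Report validity and confirmed abstinence by lag (under 7, 7 to 14, over 14 days), with lags under 7 days as a sensitivity analysis.

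The cost is two or three extra questions at a contact that already takes place, plus a card in the kit. The limitation is that the specimen-day answer is itself given with knowledge of the test, so it informs the interpretation but cannot settle individual cases. The sample size does not change.
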